### Intervention

Participants in the intervention group receive access to integrated care services in addition to routine care. The agreements under the NWpG model for IC comprise the coordination and provision of outpatient psychiatric treatment and care services through mobile multi-professional teams under professional medical supervision.

Remuneration of IC contracts is based on staggered, case-related lump sums: On the one hand, it allows for extensive design flexibility in the programme by the service provider, on the other hand, it also transfers the risk of budget responsibility to the service provider. This risk results primarily from the fact that all costs for treatment in psychiatric inpatient and outpatient clinics must be financed from the lump sum. This so-called ‘malus’ regime does not apply to services by panel psychiatrists or psychotherapists [12].

All services will be documented in the Client Socio-Demographic and Service Receipt Inventory (CSSRI), and therefore, region-specific design options can be incorporated in the final analysis.

Integrated care according to NWpG contracts under § 140a et seq of Volume V of the Social Insurance Code shares the following basic components in each region:

• individual comprehensive case management on the basis of main control centres;

• outreach mental health services including social environment through home treatment;

• low-threshold and need adapted outreach therapeutic care by multi-professional teams under professional medical supervision, including psychiatric nursing, socio-therapy, psychotherapy, psycho-education and crisis intervention;

• guarantee for 24-hours crisis support 7 days a week;

• provision of retreat areas for crisis support outside hospital settings;

• continuous cooperation with patients, relatives and legal representatives to activate existing resources and to strengthen self-help potentials (empowerment) of those affected [12,13].

### Care as usual

The range of offers for patients in the control group (CAU) is restricted to standard care. They do not receive access to the services assigned to integrated care.

Main aspects of usual care in Germany include mental health care offered in institutions such as hospitals, day-hospitals, medical practices, medical care units and outpatient clinics of psychiatric institutes. Dependent on disease severity, patients are entitled to receive special therapies such as psychotherapy or occupational therapy.

Patients have access to socio-psychiatric services, contact and counselling centres and self-help groups. In some cases, patients experience additional support from nurses, social workers or crisis support teams. In sum, offers of mental health services are wide-ranging but they vary from place to place.

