## Methods/design

### Study design

Although the randomised clinical trial is considered the gold standard for examining the efficacy of mental health care interventions, legal and organisational aspects prevent this design being applied in the current study: The implementation of integrated care programmes took place on the legal basis of the German social code which authorises the health insurances to define the criteria for the eligibility of patients to enrol in integrated care programmes. In addition, the social code gives patients the right to be informed by sickness funds about the opportunity to enrol in an integrated care programme. If a patient fulfils the eligibility criteria, he or she will be informed by the health insurance and asked for the permission to transmit his or her contact data to the local integrated care provider. After the patient gives his or her permission to the sickness fund the local service provider contacts the patient and invites him or her to attend an informative meeting. On the basis of this interview the service provider decides if the patient will be offered enrolment or not. Finally, the patient decides whether to enrol or not.

Therefore, we decided to design this study as a prospective observational controlled trial comparing patients with severe mental disorders enrolled in an NWpG integrated care programme with patients who received standard care in five federal states (Schleswig-Holstein, Northrhine-Westfalia, Berlin, Saxony and Bavaria) covering a broad range of catchment areas with different levels of urbanization, with different local mental health service systems and with different providers of ACT services. Trial duration is 18 months. Data will be collected at baseline and there will be three follow-ups after 6, 12 and 18 months.

Due to preference-based allocation blinding of patients is not feasible. Furthermore, it is not possible to blind the research associates because they would be unblinded at the latest documenting integrated care service use in the Client Socio-Demographic and Service Receipt Inventory (CSSRI).

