### Sample Size calculation

The sample size calculation is performed for the change in the empowerment total score over 18 months. An effect size of f = 0.2 was assumed to be clinically relevant for the within-between interaction of group*time in repeated-measurements ANOVA with two groups and four time-points of measurement.

Based on this effect size, a power of 0.90, and an alpha level of 0.05, a total sample size of n = 350 is needed. Sample size was further estimated based on a drop-out rate of 30 %, according to experience from the ELAN-study [27,28]. Based on this assumption, a total of 500 patients will be recruited for visit 1. The sample size was calculated using G-Power.

All participating patients will be asked to nominate a relative/informal carer who has regular contact with the patient and who supports the patient with regard to disease-related burden. It is expected that relatives/informal carers of about 50 % of patients will participate in the study. Thus, the sample size for persons of reference will be equal to n = 250. Using a repeated-measurements design with four time-points of measurements this sample size will concede the demonstration of an effect with effect-size f = 0.2 and a significance level of alpha = 0.05 with a power greater than 0.75.

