### Trial inclusion and exclusion criteria

According to the eligibility criteria for the enrolment in the NWpG care programmes patients will be included in the study if they have been diagnosed as having a mental illness of the categories F20-F29, F30-F39, F40-F48, F50, F60-F62, F68-F69 and F91- F94 after ICD-10 during the last 12 months. Patients with a primary diagnosis of substance use disorder (F10-F19, ICD-10) will be only included if they have a psychotic disorder due to substance use.

In addition, patients should have either had a psychiatric inpatient admission or an ambulatory prescription of antipsychotic, anxiolytic or antidepressant drugs during the last 12 months.

Patients must be in the age range of 18 to 80 years, and patients with a care level are excluded.

Group allocation is performed on the basis of the type of care provision intended for the coming 18 months.

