### Trial consent procedure

Patients interested in the study can choose either to contact the research associates themselves or to sign a written consent form that contact data can be submitted from cooperating psychiatric health institutions to the research associate and that the research associate is allowed to call the patient.

At the beginning of visit 1, patients will be informed once more with verbal and written information regarding the study, and patients are asked to give written informed consent if they agree to participate in this study. This will be done by local research associates.

Patients are informed that they can withdraw at any time without having to disclose reasons.

Registration in the integrated care programme occurs completely independent of patients’ decision to participate in the study or not.

Patients are asked to nominate an informal carer/relative who can be interviewed with patient approval. Participation of relatives/informal carers requires the written consent of the patient and of the person of reference him- or herself.

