#### *Statistical analysis*

The primary outcome is the change in empowerment total score of EPAS over 18 months. Normal distribution is assumed. This will be checked, and if found to be lacking than appropriate solution strategies will be applied. Data analysis for the primary outcome will be performed using analysis of variance with repeated measurements with a time effect, a group effect and an interaction effect between time and study group.

In addition, secondary analysis for the primary outcome will include a per-protocol (PP) approach. The PP population will exclude all subjects in the ITT population who meet any of the following criteria:

– change of study group during study process

– non-compliance or infrequent use of integrated care by volunteers in the IC group

– more than four weeks between registration to integrated care and visit 1 for patients in the IC group

– visit 2, visit 3 and visit 4 were outside initially planned time periods (more than +/− 1 month to intended time points: 6 months, 12 months or 18 months after visit 1)

This additional analysis assesses the maximal intervention efficacy in ideal conditions based on comparable outcome measurements.

For secondary endpoints mixed-effect regression models will be used. The random effect of time as well as the interaction effect of time and study group will be adjusted for propensity scores [28].

Within the frame of health economic evaluation based on the net benefit approach, multivariate regression models for the cost-utility relation as dependent variable will be calculated adjusted for the propensity scores. The cost-utility relation is defined as the ratio of direct and indirect costs and the change in QALYs [31-34]. Change in QALYs will be calculated on the basis of EQ-5D questionnaire. All costs will be calculated from a societal point of view, for that reason total costs of care were considered and not just out-of-pocket payments. Furthermore, production losses due to time off work for those in employment will be included in the analyses.

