### Ethical considerations

The informed consent procedure is described in the section “trial consent procedure”.

All patients enjoy freedom of choice as regards their utilisation of health-related services. However, routine care provision is expanded by integrated-care specific services (e.g. hometreatment) for patients registered in IC programmes. No patient group is disadvantaged regarding clinical care. Decisions concerning medical treatment and hospitalisation are performed by independent physicians as required. There are no adverse events expected to be related to the integrated care specific services.

Allocation to study groups depends on decisions of statutory health insurances and on patients’ preferences, completely independent of the study. No costs are imposed on patients, and all patients receive 10 € per visit to cover minor expenses.

The obtained data are strictly confidential.

Source documents are specified only by code. Using that code, data are entered into the electronic database. Source documents are maintained in a locked up cabinet in a room in the bureau of the local research associates or of the research coordinator settled at the University of Ulm. Source documents are scanned and sent by mail to the research coordinator for central data-entry just after the interview. Source documents are collected at study sites over two to three months, and will then be shipped to the research coordinator.

The research coordinator oversees the whole study procedure, and she receives progress reports of the project in each centre, if necessary, to make decisions with regard to recruitment strategies or undesired events.

The study is being conducted in compliance with the Declaration of Helsinki 2013.

It has been approved by the Ethics Committee of the University of Ulm on 3^rd^ May 2013 (application number: 129/13 and by the Ethics Committee of the TU Dresden on 30^th^ September 2013 (application number: EK 259072013).

This trial is registered with DRKS (German Clinical Trials Register) and ICTRP (International Clinical Trials Registry Platform) with the identifier DRKS00005111.

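### Usual care is described as having no access to integrated care, although group change is foreseen, and the only analysis that addresses it deletes group-changers outright

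*Protocol article*

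**What the plan says.** The Care as usual section restricts controls to standard care and says of them: "They do not receive access to the services assigned to integrated care".

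Other sections describe a looser arrangement:

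- **Trial inclusion and exclusion criteria:** "Group allocation is performed on the basis of the type of care provision intended for the coming 18 months". The clinical criteria for study entry are those of the IC programme, so controls meet them too.
- **Trial consent procedure:** "Registration in the integrated care programme occurs completely independent of patients’ decision to participate in the study or not".
- **Ethical considerations:** "All patients enjoy freedom of choice as regards their utilisation of health-related services".
- **Study design:** "the social code gives patients the right to be informed by sickness funds about the opportunity to enrol in an integrated care programme". The same paragraph limits that route: "On the basis of this interview the service provider decides if the patient will be offered enrolment or not".
- **Statistical analysis:** the per-protocol (PP) population removes from the ITT population anyone with a "change of study group during study process".

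The main analysis is ITT (Planned analysis). The sample size section makes one allowance: "Sample size was further estimated based on a drop-out rate of 30 %, according to experience from the ELAN-study". IC use is to be documented in the service receipt inventory, the CSSRI (Study design; Intervention).

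**The concern.** The comparison of interest is IC against standard care. If some controls enrol in IC during the 18 months, the ITT contrast becomes IC from the start against usual care with later IC possible. Those controls' IC contacts and costs would also fall on the usual-care side of the utilisation and cost results. That can be a legitimate question, but it is not the one the Care as usual section describes. A reader would then look to a supporting analysis for the contrast without switching.

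The PP set is the only analysis offered for this. It selects patients on something that happens after baseline. Controls who seek IC because they are doing badly, or IC patients who leave because they are doing well or badly, are not a random subset. The PP set also combines group change with poor uptake of IC, late first visits and visits outside the time window, so the effect of switching cannot be isolated. At stake is whether a small or null result can be interpreted.

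**Working it through.** **1. Is the absence of access a fact or an intention?** The Care as usual section states it as a fact. The inclusion criteria fix group by intended care, the consent section says the study neither grants nor blocks registration, and the PP list names group change. Read together, these describe usual care at entry with later change possible. The documents give no rate of change and no direction.

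**2. What the PP rule discards.** Visits are at 0, 6, 12 and 18 months. A control who registers for IC between months 6 and 12 has two of four visits recorded under usual care, and one who registers between months 12 and 18 has three of four. The rule removes all of them.

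**3. What the PP rule does to the estimate.** Let a share s of controls switch, and suppose that without switching their mean EPAS change would have been lower by d than the mean μ of the other controls.

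- Mean for all controls had nobody switched: (1 − s)μ + s(μ − d) = μ − s·d
- Mean for the PP controls: μ
- Bias in the control mean: s·d

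At s = 10% the bias is one tenth of d, and at 20% one fifth. Its sign follows the sign of d, which the documents do not give. The same algebra applies to IC patients who leave.

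Lost numbers matter less. With 175 patients per group (half of 350), removing 10% of controls leaves an effective total of 4 × 175 × 157.5 / 332.5 = 331.6 and power 0.877. Removing 20% leaves 4 × 175 × 140 / 315 = 311.1 and power 0.853. The main weakness of the rule is selection.

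**4. The stated sample size.** Inputs from the sample size section: f = 0.2 for group × time, two groups, four time-points, alpha 0.05, power 0.90, N = 350, drop-out 30%. I used a noncentral F test with df1 = 3, df2 = 3(N − 2) and λ = f²N.

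- At N = 350: λ = 0.04 × 350 = 14.0, power 0.895. Power of 0.90 is reached at N = 356.
- Drop-out: 350 / 0.70 = 500.

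The stated figures reproduce closely. No term for switching enters them.

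**5. Power if f = 0.2 describes the unswitched effect.** The switching rates are assumptions. Under full dilution f becomes 0.2(1 − s), with every switcher counted as having the other group's course from baseline. Under half dilution f becomes 0.2(1 − s/2). N = 350 throughout.

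| Switching s | f, full | Power, full | f, half | Power, half |
|---|---|---|---|---|
| 0% | 0.200 | 0.895 | 0.200 | 0.895 |
| 5% | 0.190 | 0.859 | 0.195 | 0.878 |
| 10% | 0.180 | 0.815 | 0.190 | 0.859 |
| 20% | 0.160 | 0.707 | 0.180 | 0.815 |
| 30% | 0.140 | 0.578 | 0.170 | 0.765 |

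If f = 0.2 is instead the ITT effect with whatever switching occurs, only the first row applies.

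**The case against.** The sections can be read as one coherent scheme: usual care at entry, deviations recorded in the CSSRI, ITT as the main analysis and PP as a secondary one. ITT suits the routine-care question that the article declares. Details of a weighted analysis would normally belong in the statistical plan, which the article says will be written separately.

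Much of this stands, and it rules out several stronger readings:

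- **That controls have a right to enrol in IC.** The documents give a right to be informed. Enrolment then depends on the insurer's criteria, the provider's offer and the patient's decision. Only some insurers run such programmes, and some controls will already have declined IC (Trial recruitment process).
- **That the comparator is in fact contaminated.** A PP exclusion shows that group change was thought possible, not that it happens often. It also covers patients leaving IC.
- **That the 0.90 power is wrong.** The article presents f = 0.2 as a clinically relevant effect and never as the effect under full separation.
- **That the losses under full dilution are the expected ones.** They are near the worst case, because a switcher cannot have the other group's course from baseline. Multiple imputation also lets patients who drop out contribute: at an illustrative effective N of 400, full dilution at 10% gives power 0.868.

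The objection does not rescue the PP rule. Whole-patient removal of group-changers is fixed in the article itself, so this is a stated choice and not a detail left to the statistical plan.

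**Conclusion.** The point holds in a limited form. The flat statement about access conflicts with the sections on allocation, consent, freedom of choice and PP exclusions, so the comparator is not assured to be IC-free. The weakness that merits a change is the PP rule. It conditions on post-baseline behaviour plausibly related to outcome, discards valid pre-switch visits, and can bias the unswitched contrast by s·d in a direction the documents do not reveal.

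The ITT analysis is sound for the declared question. The power statement needs clarifying, not correcting. If f = 0.2 is the unswitched effect, power is about 0.82 to 0.86 at 10% switching and 0.71 to 0.82 at 20%, for full to half dilution. These figures rest on assumed rates and on N = 350.

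**What to change.** 1. **Statistical analysis.** Keep ITT as the main analysis. For group change in either direction, replace whole-patient deletion with an analysis that keeps each patient's visits up to the switch and censors later ones. Weight by the inverse probability of not switching, given EPAS, HoNos and service use at the previous visit. Report it separately from the other PP criteria, so that the effect of switching can be seen on its own.
2. **Care as usual.** Describe controls as patients with no IC enrolment intended at entry, and record any later enrolment with its date.
3. **Sample Size calculation.** Say whether f = 0.2 is the ITT effect including switching, in which case 0.90 stands, or the unswitched effect. In the latter case give power at 5%, 10% and 20% assumed switching.

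The cost is some wording, a registration date, and one weighted supplementary analysis on outcomes already collected. The weights add some variance, and they remove bias only as far as the measured variables predict switching. No increase in enrolment is proposed.

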### Measurement instruments

The primary outcome will be measured by means of the questionnaire for the assessment of empowerment in patients with affective and schizophrenic disorders (EPAS). The EPAS measures empowerment as the patient’s perceived opportunity to control their own living circumstances on five dimensions: “daily living”, “social relationships and sexuality”, “psychiatric treatment”, “hope and self efficacy” and “self esteem”. Additional subscales are available for patients who are employed and for parents of minor children. The EPAS core module has 33 items and a Cronbachs Alpha of .94 was obtained for the total scale [14].

The secondary outcome measures include 1) reduction in psychosocial and clinical impairment using HoNos [Health of the Nation outcome scale] [15-18], 2) improvement of subjective quality of life using WHO-QoL-BREF [World Health Organisation Quality of Life-short version] [19], 3) reduction of unmet needs for psychiatric and psychosocial services using CAN-EU [Camberwell Assessment of Need-European Version] [20,21], 4) increase in satisfaction with psychiatric treatment using ZuF8 [questionnaire to treatment satisfaction] [22,23], 5) reduction of utilisation of stationary and simultaneous increase in utilisation of ambulatory medical and psychosocial services using CSSRI [Client Socio-Demographic and Service Receipt Inventory] [24], 6) reduction of direct and indirect healthcare costs using CSSRI [24], 7) reduction of costs of recovering a “healthy” year of life (QALY) using EQ-5D [Euro Quality of Life – 5 dimensions] [25].

An additional study-specific questionnaire will be used at visit 2, 3 and 4 to gain ancillary information as regards the importance of and the satisfaction with local community mental health services from the patients’ perspective.

There is the following set of outcome measures for relatives and informal carers: 1) Change in perception of burden related to support of patient suffering serious mental illness using IEQ [Involvement Evaluation Questionnaires] [26], 2) change in subjective quality of life using WHO-QoL-BREF [19] and 3) change in satisfaction with psychiatric treatment using ZuF8 [22,23].

### Sample Size calculation

The sample size calculation is performed for the change in the empowerment total score over 18 months. An effect size of f = 0.2 was assumed to be clinically relevant for the within-between interaction of group*time in repeated-measurements ANOVA with two groups and four time-points of measurement.

Based on this effect size, a power of 0.90, and an alpha level of 0.05, a total sample size of n = 350 is needed. Sample size was further estimated based on a drop-out rate of 30 %, according to experience from the ELAN-study [27,28]. Based on this assumption, a total of 500 patients will be recruited for visit 1. The sample size was calculated using G-Power.

All participating patients will be asked to nominate a relative/informal carer who has regular contact with the patient and who supports the patient with regard to disease-related burden. It is expected that relatives/informal carers of about 50 % of patients will participate in the study. Thus, the sample size for persons of reference will be equal to n = 250. Using a repeated-measurements design with four time-points of measurements this sample size will concede the demonstration of an effect with effect-size f = 0.2 and a significance level of alpha = 0.05 with a power greater than 0.75.

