### Trial status

Currently recruiting status:

N_current_[patients, IC] = 228

N_current_[patients, CAU] = 170

N_current_[persons of reference, IC] = 105

N_current_[persons of reference, CAU] = 58

as of 7^th^ may 2014

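### The power above 0.75 claimed for relatives holds only if practically all 250 recruited relatives complete; no loss is allowed for, although patients are sized for 30% drop-out

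*Protocol article*

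**What the plan says.** All the figures are in *Sample Size calculation* in the protocol article.

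- **Patients.** At f = 0.2 for the group-by-time interaction (two groups, four time-points), alpha 0.05 and power 0.90, the section asks for 350 patients. It then adds an allowance: "Sample size was further estimated based on a drop-out rate of" 30%, which leads to 500 recruited at visit 1.
- **Relatives.** The next paragraph starts from uptake: "It is expected that relatives/informal carers of about 50 % of patients will participate in the study". From this it concludes: "Thus, the sample size for persons of reference will be equal to n = 250". For that number and four time-points it claims "the demonstration of an effect with effect-size f = 0.2 and a significance level of alpha = 0.05", "with a power greater than 0.75".

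*Trial recruitment process* confirms that 250 is the number of relatives to be recruited, half the number of patients. *Data collection/management process* gives relatives the same four assessments as patients, at baseline and at 6, 12 and 18 months, mostly by questionnaires returned by post. No drop-out allowance for relatives appears anywhere in the article.

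**The concern.** Two bases are used in one section. The patients' power is quoted for those expected to remain after drop-out. The relatives' power is quoted for everyone recruited, as if none would be lost over 18 months. A reader who compares 0.90 with 0.75 will assume that they mean the same thing, and they do not.

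The relatives' outcomes are secondary to the patient comparison, but they are a declared aim. The *Background* says that effects on relatives' burden and quality of life will be evaluated, and it raises the possibility that moving care out of hospital adds to their burden. If the stated power is too high, readers will misjudge how likely the study is to detect an effect of the size it names.

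**Working it through.** **Inputs** (all from *Sample Size calculation* unless noted): f = 0.2, so f² = 0.04; alpha = 0.05; two groups and four time-points, so the interaction has 3 numerator degrees of freedom; 350 patients needed, power 0.90, 30% drop-out, 500 recruited; 250 relatives, power above 0.75. That the 250 are recruits comes from *Trial recruitment process*. The article does not name the test behind the relatives' figure. I take it to be the same interaction, and step 2 supports this.

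**Formula.** Power = P(F′ > F crit), where F′ is noncentral F with 3 and df2 degrees of freedom and noncentrality λ. Three close variants were used:

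- A: λ = f² × N, df2 = 3(N − 2)
- B: λ = f² × (N − 2), df2 = 3(N − 2)
- C: λ = f² × (N − 2), df2 = N − 4

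**Step 1: the patients' figure.** At N = 350, λ is 0.04 × 350 = 14.0 (A) or 0.04 × 348 = 13.92 (B, C). Power is 0.895, 0.893 and 0.891, against the stated 0.90. The inflation is 350 / 0.70 = 500, as stated.

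**Step 2: the relatives' figure.** At N = 250, λ is 10.0 (A) or 9.92 (B, C). Power is 0.759, 0.755 and 0.750, against the stated value above 0.75. One convention therefore accounts for both claims. Other settings do not: with λ = f² × N × 4 / (1 − 0.5), that is four time-points and a correlation of 0.5, power at N = 350 is about 1.00; a test of the group main effect gives 0.96 to 1.00 at N = 350 and 0.88 to 1.00 at N = 250.

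**Step 3: how much loss the claim can bear.** Power first reaches 0.75 at N = 246 (A) or 248 (B); under C it is 0.7499 at N = 250. At N = 245, a loss of 2%, all three variants are below 0.75 (0.749, 0.745, 0.740).

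**Step 4: power after loss.** The drop-out rates are assumptions, because the article gives none for relatives. Completers = 250 × (1 − drop-out).

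| Assumed drop-out | Completers | Power, variant A | Power, variant C |
|---|---|---|---|
| 0% | 250 | 0.759 | 0.750 |
| 5% | 237.5 | 0.734 | 0.725 |
| 10% | 225 | 0.708 | 0.698 |
| 20% | 200 | 0.651 | 0.640 |
| 30% (patients' rate) | 175 | 0.586 | 0.573 |
| 40% | 150 | 0.514 | 0.500 |

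Variant B lies between A and C throughout (0.581 at 175).

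**Step 5: what 175 completers can detect.** At N = 175 and f = 0.24, power is 0.761 (A), 0.756 (B) and 0.749 (C). Power 0.75 is therefore reached only at f of about 0.24, not 0.2.

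**The case against.** **The sentence is correct as written.** It is conditional: 250 relatives give power above 0.75, and they do. This stands, and the point is not an arithmetic error. The figure is nevertheless attached to the number recruited, and nothing tells the reader that it assumes complete follow-up.

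**No drop-out rate for relatives is given, and theirs may differ from the patients'.** This also stands. Relatives volunteer themselves and mostly return questionnaires by post; their loss could be lower or higher than 30%. A reader might infer that the power of the relatives' comparison simply is 0.58. The article does not support that: 0.58 results from carrying over the patients' rate, and it must be shown as one point in a range. The conclusion that power falls below 0.75 does not depend on 30%, since a loss of 2% is enough.

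**Multiple imputation keeps incomplete cases in the analysis.** It does, under *Dealing with missing values*, and counting completers only treats every drop-out as contributing nothing, which is somewhat pessimistic. Imputation does not, however, restore the information lost, and the article plans it while still inflating the patient sample for drop-out.

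**The recruitment counts.** *Trial status* lists 105 relatives in integrated care and 58 under "persons of reference, CAU", 163 in all for 228 + 170 = 398 patients, or 41%. A reader might infer that uptake will miss 50% and project a still lower power. That is not supported: the count was taken during recruitment, and relatives enrol after their patient, because they are nominated at visit 1 and then asked to make contact themselves.

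**Misuse of a null result.** A reader might also infer that the study will treat non-significance as proof of no added burden. Nothing in the article plans this.

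**A condensed article may leave retention assumptions to the full protocol.** That is possible. But the article itself states a power for relatives and ties it to a recruitment number, so the figure should carry its condition.

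**Conclusion.** The point holds in a limited form. The relatives' power above 0.75 is right for 250 complete relatives and has almost no slack: it needs about 246 to 250 of the 250 recruited. No allowance is made for loss over 18 months, while the patients in the same section are sized on completers after 30% drop-out.

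The shortfall depends on a rate that the article does not give. It is small at 5% loss (about 0.73) and substantial at the patients' rate (0.57 to 0.59, a chance of about 42% of missing f = 0.2). These values rest on the relatives' test being the same group-by-time interaction, and on losses being counted as in the patients' calculation. The omission and the lack of slack are firm; any single value for the power after drop-out is not. The patients' primary comparison is unaffected.

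**What to change.** In *Sample Size calculation*, restate the relatives' power on expected completers and label the drop-out rate as an assumption. For example: *With 250 relatives recruited and, if drop-out is 30% as assumed for patients, about 175 completers, power at f = 0.2 is about 0.58 (about 0.71 at 10% and 0.65 at 20% drop-out); with 175 completers, power 0.75 is reached at f of about 0.24.*

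Update the statement with the number of relatives finally enrolled.

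The cost is one reworded sentence and a less favourable figure. No extra recruitment is needed, and neither the design nor the analysis changes.
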